### Measures

Through process evaluation, the CARES-REACH program implementation will be assessed to ensure it is proceeding as planned (e.g., meeting the goals and timelines for accomplishing each component of the program implementation). Guided primarily by the CFIR and RE-AIM frameworks, we developed and implemented a Readiness Evaluation Assessment Level (REAL) survey with FQHC institutional leaders, cancer control champions, and a diverse group of providers (e.g., medical assistants, nurses, Advance Practice Practitioners [ARNP/PA], and physicians) from various clinic locations to solicit feedback about how to assess implementation processes including facilitators/impediments of intervention implementation, at three time points (baseline, mid-point and at the end of project implementation). This questionnaire solicits readiness feedback from leaders, providers, and champions (key stakeholders involved in the implementation of CRC screenings) from our two partnering FQHC organizations at three timepoints. The information gained will provide context for study findings (i.e., screening uptake and trends) and contribute to sustainability planning, scale-up, and maintenance. Through this process and conclusions, we will continually refine and improve processes and determine whether the current approaches effectively bring about the desired outcome (i.e., improvements in clinic CRC screening rates).

Notably, the significance of the proposed work for FQHC systems is potentially high for improving their overall UDS screening measures (annual rates) over time. UDS is a crucial quality and performance measure in primary care used by FQHCs to calculate the percentage of patients receiving a recommended (prevention) care service, such as CRC screening [94]. According to recent data from our two participating FQHC organizations (Central Florida Health Care (CFHC) and MCR Health (MCR)), organization-wide UDS measures from 2015 to 2017 ranged from 26–38%, indicating that a unique window of opportunity exists for improvement. Table 5 outlines the constructs and outcome metrics aligned with the RE-AIM and CFIR implementation science frameworks.

### Statistical and Data Analysis

A longitudinal linear mixed model with 3-year CRC screening rates will be used to analyze data for Aim 1. The linear mixed model to assess changes in UDS will include 42 (= 14 clinics x 3 years) CRC screening rates due to the stepped wedge randomization of these clinics. The model will use independent variables: intervention (fixed), clinic (random), rural (urban = reference group; fixed), and time (fixed), using an unstructured variance-covariance model. The model is expected to provide an estimate of the secular time trend of about 2.7% per year on a national level (in 2014–2016). For the stepped-wedge portion of the study, we will have 83.6% and 97.5% power to detect a difference of 4% and 5% in the CRC screening rates between intervention and non-intervention clinics, assuming an intracluster correlation coefficient (ICC) of 0.013, where the power is minimized (obtained from PASS15).

For Aim 2, the analysis will include a logistic regression model, with successful screening as the dependent variable. The independent variables will consist of patient, practice, and organization. Data for all patients seen at participating clinics in a given calendar year will be analyzed by year and clinic setting to examine trends in screening rates at the individual patient level. To show their screening rate patterns, we will ascertain individual-level data with a non-PHI patient ID. We will also estimate the proportion of FIT-screened patients who complete FIT screening in the intervention’s initial wave (intervention vs. control) and subsequent year(s). We will estimate the probability of initiating screening in years 2 and 3 for patients seen in the clinic but not screened in previous years.

For aim 3, we will evaluate the intervention’s success and how to expand its reach to other community health systems. The RE-AIM (59) and CFIR (60) frameworks will serve as guides for this evaluation of the intervention’s implementation process (organization-wide implementation experience) and resource requirements. The implementation process will be analyzed using both qualitative and quantitative methods. Through process evaluation, we will assess whether the CARES-REACH study implementation is proceeding as planned through tracking documentation, detailing process changes, and regular champion interactions.

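### The two power figures for Aim 1 (83.6% at 4 points, 97.5% at 5 points) do not fit one standard error at any conventional alpha, and the claim that power is at its minimum holds only if clinic effects are constant across years

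*Protocol article*

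**What the plan says.** In the Protocol article, Statistical and Data Analysis, the Aim 1 model "will include 42 (= 14 clinics x 3 years) CRC screening rates", with terms "intervention (fixed), clinic (random), rural (urban = reference group; fixed), and time (fixed), using an unstructured variance-covariance model". The power claim for the stepped-wedge part of the trial is "we will have 83.6% and 97.5% power to detect a difference of 4% and 5% in the CRC screening rates"; the comparison is of clinics with and without the intervention. Both figures rest on a single value of the correlation, which the article describes as an "intracluster correlation coefficient (ICC) of 0.013, where the power is minimized", and it names PASS15 as the software. The section gives no alpha, no base rate for the calculation and no number of patients per clinic-year.

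Two other places bear on the check. Table 2 has 0, then 7, then 14 of 14 clinics under intervention over the first three years. The Measures section reports that "organization-wide UDS measures from 2015 to 2017 ranged from 26–38" percent in the two organizations.

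**The concern.** Power at two effect sizes from the same design, correlation and software run should come from essentially the same standard error, so either figure fixes the other. These two do not fix each other. At least one printed number, either a power or a difference, is therefore wrong, rounded too coarsely, or based on an input that is not shown.

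The phrase about minimized power adds a second problem. A reader will take it as a worst case. In a stepped-wedge model it is one only if the clinic effect does not vary between years.

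This sentence is the article's only statement of what the primary analysis can detect. A reader who judges a null or small effect against it needs it to be right.

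**Working it through.** **Inputs.** The powers, differences, correlation of 0.013 and 14 × 3 layout come from Statistical and Data Analysis. The allocation of 7 clinics per wave comes from Table 2, and the base-rate range of 26–38% from Measures. Assumed because not stated: two-sided alpha 0.05 (others tried), patients per clinic-year *m*, and cluster autocorrelation.

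**Step 1: do the two figures share a standard error?** Power = Φ(δ/SE − z), with z = 1.960, z(0.836) = 0.978 and z(0.975) = 1.960.

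- From 83.6% at 4 points: SE = 4/(1.960 + 0.978) = 1.361. At 5 points, Φ(5/1.361 − 1.960) = 95.7%, against 97.5% printed.
- From 97.5% at 5 points: SE = 5/(1.960 + 1.960) = 1.276. At 4 points, Φ(4/1.276 − 1.960) = 88.0%, against 83.6% printed.

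Rounding of the powers does not explain this: any value that prints as 83.6% gives 95.6–95.7% at 5 points.

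**Step 2: other references.** Starting each time from 83.6% at 4 points:

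| Reference | Power at 5 points |
|---|---|
| Two-sided 0.10 (one-sided 0.05) | 94.9% |
| Two-sided 0.05, noncentral t, 6–40 df | 95.4–95.7% |
| Two-sided 0.05, normal | 95.7% |
| Two-sided 0.01, normal | 96.9% |
| Two-sided 0.005, normal | 97.3% |

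The pair is met exactly only at a two-sided alpha of about 0.003. Letting p(1 − p) follow the alternative makes the fit worse: from 26–38% the variance rises with the effect, which lowers power at 5 points relative to 4.

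**Step 3: which differences would fit?** The ratio of the z-sums is 2.938/3.920 = 0.7495. The printed differences have ratio 4/5 = 0.80; differences of 3 and 4 have 0.75. With SE = 3/2.938 = 1.021, power is 83.6% at 3 points, 97.5% at 4 and 99.8% at 5.

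**Step 4: is 83.6% at 4 points attainable?** For 14 clinics, 7 per wave and 3 years, the Hussey-Hughes variance is Var = (2/7)·s²(s² + 3τ²)/(s² + 2τ²), with s² = p(1 − p)(1 − ICC)/m and τ² = ICC·p(1 − p). Take p = 0.32 and an assumed m = 485. Then s² = 0.2176 × 0.987/485 = 0.000443 and τ² = 0.013 × 0.2176 = 0.002829. This gives SE = 1.361 points, hence 83.6% at 4 points and 95.7% at 5. The 4-point figure can therefore be reached with ordinary inputs; the 5-point figure does not follow from it.

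**Step 5: the minimum over ICC.** Use the same p and m. Cluster autocorrelation (CAC) below 1 moves the part ICC·p(1 − p)·(1 − CAC) of the clinic variance from τ² into s². Power at 4 points:

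| ICC | CAC 1 (constant) | CAC 0.9 (assumed) |
|---|---|---|
| 0.005 | 84.6% | 76.9% |
| 0.010 | 83.8% | 68.2% |
| 0.013 | 83.6% | 63.9% |
| 0.020 | 83.6% | 55.6% |
| 0.050 | 84.4% | 35.5% |

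With constant clinic effects there is a flat interior minimum around 0.013–0.02, so the printed remark is coherent in that model. At CAC 0.9 power falls steadily as ICC rises, and 0.013 is not a minimum. At ICC 0.013, power at 4 and 5 points is 73% and 89% for CAC 0.95, 64% and 83% for 0.9, and 51% and 70% for 0.8. These values illustrate the direction; the article gives neither m nor CAC.

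**The case against.** The strongest reply is that alpha, base rate and clinic size are not printed, that an article may leave them to the full protocol, and that the forward gap is only 1.8 points of power. A single SE of 1.33 gives 85.3% and 96.4%, both within 2 points of print. The differences may also have been rounded to whole points: 83.6% and 97.5% fit 3.75 and 5 points (5 × 0.7495 = 3.75).

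This limits the finding but does not remove it. Leaving out inputs is not the complaint; the complaint is about the printed numbers. Software powers given to 0.1 point should agree with each other, and SE 1.33 reproduces neither figure. If a 3.75-point difference was printed as 4, that too needs correcting, because the rounding moves power at 4 points from 88.0% to 83.6%.

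A reader might infer more than the documents support:

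- **That the differences were certainly shifted by one point.** The 3:4 ratio is suggestive. Supporting it by arguing that a minimum at exactly 0.013 implies about 910 patients per clinic-year, which would make 83.6% at 4 points impossible, does not work. Power is almost flat in ICC, so 0.013 does not identify the clinic size, and step 4 reaches 83.6% at 4 points with ordinary inputs.
- **That the trial is underpowered.** The losses in step 5 rest on assumed values. With about 910 patients per clinic-year, a base rate of 0.35 and an added clinic-by-year SD of 1 point, power at 4 points is about 91%, above the printed 83.6%; at an SD of 2 points it is about 69%. Nothing in the article selects among these.
- **That the remark on minimized power is false.** It is attached to the ICC and is true in the constant-effect model. The planned unstructured covariance need not assume constancy, so the remark concerns planning power, not the precision of the final analysis.

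**Conclusion.** The power statement needs correction. Taken as printed, 83.6% at 4 points and 97.5% at 5 points do not come from one standard error at any conventional alpha. At two-sided 0.05 the error is 1.8 points of power if the 4-point figure is right (95.7%, not 97.5%) or 4.4 points if the 5-point figure is right (88.0%, not 83.6%). Differences of 3 and 4 points would reconcile the pair, which is a possible cause only. The documents do not show which number is wrong.

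The remark on minimized power is a minimum over ICC under constant clinic effects, not a general worst case. The direction of that qualification is certain; its size is unknown.

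Severity is minor to moderate. Every consistent reading of the pair leaves power above 80% at 4 points under the constant-effect model, and under the 3-and-4-point reading the article understates its power. The conclusion rests on a common standard error for both differences and an alpha in the usual range.

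**What to change.** Recheck the PASS run and restate the pair as it shows:

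- 83.6% and 95.7% at 4 and 5 points;
- 88.0% and 97.5% at 4 and 5 points; or
- 83.6% and 97.5% at 3 and 4 points.

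These values assume two-sided 0.05. If the run used another alpha or unrounded differences, print those instead. Give the alpha, base rate and patients per clinic-year beside the result.

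Qualify the remark on minimized power as a minimum over ICC that assumes clinic effects are constant across years, and note that clinic-by-year variation can lower power. A short sensitivity range over that variation would help.

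The cost is one re-run and a few words. No clinics, patients or design features change.

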**Methods:**

Informed by a community-based participatory research (CBPR) framework and enriched by implementation science approaches, CARES-REACH features a stepped wedge design with extension for maintenance to support an implementation strategy focused on multiple levels: organizational, provider, and patient levels that entail processes to boost initial and repeat screening among average risk and age-eligible adults. This multilevel study entails the implementation of a core set of evidence-based interventions (EBIs) that include low literacy patient education (English, Spanish, and Haitian Creole language); provider education, system-wide electronic medical record (EMR) tools including provider prompts and patient reminders, FIT (fecal immunochemical test) kit distribution, plus an organization-wide cancer control champion who motivates providers, coaches and navigates patients, and monitors system-wide CRC screening activities.

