Recent studies, including our team’s preliminary investigations in community clinics (15–17), have demonstrated that CRC screening using a single-application FIT is well received by both patients and providers and can lead to initial screening rates of 80% (15–26). Our prior work has demonstrated high initial FIT uptake and endorsed the use of FIT paired with EBIs, such as videos, brochures, etc. (15–17, 27). Further, including coaches/navigators often increases patient engagement, mitigates obstacles, and serves as a way to bring resources for improving health outcomes for chronic diseases (54, 55). Attention to culture, literacy, and language (including English, Spanish, and Haitian Creole) to support CRC educational messaging is also a prerequisite for effective patient education. (56, 57, 58). The evidence-based interventions (EBIs) in CARES-REACH are based on characteristics and components that have been shown to be feasible and effective, such as using electronic health records (EHR) to identify patients needing screening and providing culturally, linguistically, and literacy-level-appropriate information in a clear manner (28). Evidence-based interventions, such as providing accessible FIT kits, have also been supported by several studies as an approach to removing access obstacles (10, 11, 29). Other effective educational EBIs include patient-directed videos, pamphlets, reminder letters/messages, and provider/nursing reminders and prompts (28).

FIT requires annual repeat testing to optimize clinical benefits (30–35), but repeat screening rates often decline sharply following initial screening (22%–60%) (19, 20, 36). This highlights the importance of implementing evidence-based intervention strategies to encourage both initial and repeat screening. However, multiple intersecting influences can impact the implementation of evidence-based practices in clinic settings. Strategies in prior studies were heavily led by the research team (15, 37–40); therefore, the next step is a more pragmatic trial with an implementation science-based approach. As such, a pressing gap remained to expand this work to broader geographically dispersed populations, including rural locations that may benefit from cancer screening. Therefore, our ‘real world’ implementation project, CARES-REACH, is intended to address this gap and assess intervention impact on annual FIT adherence over time.

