### Cancer Control Champion

A key component of CARES-REACH is the cancer control champion hired by each FQHC to work throughout the organization from a central location while leveraging the system-wide communication technology and the EMR. This centralized role expands the potential reach of CRC screening interventions, especially in settings such as FQHCs, where resources and efforts to improve cancer-related inequalities might be limited at individual clinic sites. The Cancer Control Champions have been hired and trained and bring backgrounds in healthcare, education, and/or nursing. Originally conceived as one person filling the role of champion, one FQHC organization has implemented a Champion Distributive Model whereby one individual is identified as the lead champion with other team members contributing supporting expertise such as quality improvement, outreach, or education.

Thus, the cancer control champion is pivotal to the CARES-REACH intervention at each of the three levels: 1) organization or systems level to prioritize CRC screening and optimize EMR systems for implementation of CRC screening; 2) provider education (initial and annual booster training) and feedback to support evidence-based CRC screening patient education, recommendation and distribution of FIT kits; and 3) patient level (coaching and addressing patient-specific barriers for individuals who do not return a FIT kit within 90 days of distribution). This latter level represents an approach supported by increasing evidence that is predicated on patient activation, education, and support for promoting both initial and repeat screening (15–26, 36, 54–57). Our evaluation efforts include understanding the infrastructure, resources, and processes for role sustainability.

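### The Aim 2 intervention-versus-control comparison of FIT completion uses a denominator, FIT-screened patients, that the intervention can itself change

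*Protocol article*

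**What the plan says.** The sentence is in the Aim 2 paragraph of Statistical and Data Analysis: "We will also estimate the proportion of FIT-screened patients who complete FIT screening". It places the estimate in the intervention's "initial wave (intervention vs. control) and subsequent year(s". No other denominator is given for this contrast.

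The same paragraph says that "Data for all patients seen at participating clinics in a given calendar year will be analyzed by year and clinic setting". Its declared purpose is a description of trends. That is an all-patient denominator, but it is not attached to the FIT contrast.

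Three statements show where the intervention acts:
- The abstract's Methods list, among the core components, "FIT (fecal immunochemical test) kit distribution, plus an organization-wide cancer control champion".
- The Cancer Control Champion section includes provider education and "feedback to support evidence-based CRC screening patient education, recommendation and distribution of FIT kits".
- The same section includes "coaching and addressing patient-specific barriers for individuals who do not return a FIT kit within 90 days of distribution".

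The first two affect who receives a kit. The third affects who returns it.

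The Introduction says the project is meant to "assess intervention impact on annual FIT adherence over time". Table 5 lists initial and repeat FIT completion under Effectiveness, also without a denominator.

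**The concern.** A randomized comparison is protected when the patients counted in each arm are defined by something the intervention cannot alter. Here the denominator is described by FIT status, and raising FIT use is what the intervention sets out to do. If activated clinics give kits to patients who would not otherwise have had one, the two arms' denominators contain different kinds of patient. A difference in completion then mixes the effect of the programme with the change in who is counted.

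At stake is the reading of the FIT-specific result. The primary outcome covers all screening modalities, so it does not supply a FIT contrast to replace this one. A programme that brings more due patients to a completed FIT could show a lower completion percentage on this measure.

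**Working it through.** The article gives no rate, sample size or power for this comparison, so there is no figure to reproduce. The check has two parts.

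**1. Possible meanings of the denominator**

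- *Completed a FIT in the period.* Numerator and denominator coincide: 100% in both arms.
- *Given or ordered a kit.* Entry follows activation and is driven by kit distribution and provider education.
- *Completed a first FIT after activation, then repeats.* Entry again follows activation.
- *FIT-screened before activation, repeats in the initial wave.* Entry precedes activation, so this problem does not arise. The sentence does not state this restriction.

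**2. Size and direction under the second and third meanings**

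Notation, with shares taken among all due patients:
- a = share in the denominator under either condition
- b = share added by the intervention
- r0, r1 = completion in the first group under control and under intervention
- rn = completion in the added group

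Formulas:
- All due patients: control a·r0; intervention a·r1 + b·rn
- Within the denominator: control r0; intervention (a·r1 + b·rn)/(a + b)
- The within-denominator comparison turns negative when r1 < [(a + b)·r0 − b·rn]/a

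All inputs are assumptions. In the repeat-FIT rows, a = 0.26 and a + b = 0.38 borrow the 26–38% organization-wide UDS range under Measures. That range covers all modalities, so using it as a FIT share is itself an assumption. The values 0.60 and 0.22 are the ends of the repeat-screening range in the Introduction.

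| Meaning | a | b | r0 | r1 | rn | All due patients | Within the denominator |
|---|---|---|---|---|---|---|---|
| Kit given | 0.30 | 0.30 | 0.60 | 0.60 | 0.30 | 18.0% vs 27.0%: +9.0 | 60.0% vs 45.0%: −15.0 |
| Kit given | 0.30 | 0.30 | 0.60 | 0.70 | 0.30 | 18.0% vs 30.0%: +12.0 | 60.0% vs 50.0%: −10.0 |
| Kit given | 0.30 | 0.10 | 0.60 | 0.65 | 0.30 | 18.0% vs 22.5%: +4.5 | 60.0% vs 56.25%: −3.75 |
| Kit given | 0.30 | 0.30 | 0.60 | 0.70 | 0.60 | 18.0% vs 39.0%: +21.0 | 60.0% vs 65.0%: +5.0 |
| Repeat FIT | 0.26 | 0.12 | 0.60 | 0.60 | 0.22 | 15.6% vs 18.2%: +2.6 | 60.0% vs 48.0%: −12.0 |
| Repeat FIT | 0.26 | 0.12 | 0.60 | 0.70 | 0.22 | 15.6% vs 20.8%: +5.2 | 60.0% vs 54.8%: −5.2 |
| Repeat FIT | 0.26 | 0.12 | 0.60 | 0.80 | 0.22 | 15.6% vs 23.4%: +7.8 | 60.0% vs 61.7%: +1.7 |

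First row in full: (0.30×0.60 + 0.30×0.30)/0.60 = 0.27/0.60 = 45%. Return among patients who would have had a kit anyway is unchanged (0.60 in both arms), so the whole −15 points comes from composition.

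Fourth row: there is no reversal, yet the +5 points is not the effect in a fixed group either. Patients who would have had a kit anyway gain 0.70 − 0.60 = 10 points.

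Break-even for the repeat-FIT rows: r1 = (0.38×0.60 − 0.12×0.22)/0.26 = 0.2016/0.26 = 0.775. Below that the sign reverses; above it, it does not.

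The repeat-FIT rows treat the control clinics as still unexposed at the repeat test. Under Table 2 all 14 clinics are active from Year 2, so these rows illustrate the mechanism only.

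**The case against.** **The case for leaving it.** This is a condensed article, and an operational definition may sit in a fuller document. The sentence can be read as patients FIT-screened earlier who repeat in the initial wave, which fits the article's interest in annual repeat testing and is free of the bias. No analyst would compute the 100% version. Aim 2 is exploratory, the verb is estimate, and no test or power is attached. Completion among kit recipients is a legitimate process measure. Coaching of non-returners should raise completion, so a lower percentage in activated clinics is not a given.

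**What stands.** The limits on importance and direction stand. The appeal to brevity does not: the sentence names both a denominator and a between-arm contrast, so the point concerns what is written, not what is left out. The bias-free reading is possible but has to be supplied by the reader.

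**Stronger readings the documents do not support.**
- *That the comparison will point the wrong way.* This requires the added patients to complete less often, by enough to outweigh any gain among the others. The article gives no rates by arm, and the table above includes cases without reversal.
- *That the later-year part lacks a control group.* The parenthetical contrast attaches only to the initial wave. Later years are presented as an extension for maintenance, and no controlled claim is made for them.
- *That the "probability of initiating screening in years 2 and 3 for patients seen in the clinic but not screened in previous years" has no controls.* This depends on the numbering. Table 2 runs from Year 0 to Year 4, Table 5 counts Years 1–5, and the Aim 1 model counts three years. If the baseline is year 1, year 2 has seven clinics in each condition. That sentence claims no between-arm contrast in any case.

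**Conclusion.** The point holds in a limited form. The initial-wave contrast is either uninformative (100% in both arms) or open to selection bias, unless the group is restricted to patients FIT-screened before activation, which the text does not state. Across the assumed scenarios the result ranges from a reversal (−15 points within the denominator against +9 among all due patients) to no reversal (+5 against +21). Those sizes rest wholly on assumed kit-offer and completion rates. The loss of comparability does not: it follows from kit distribution and provider education being intervention components.

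A reader might infer that the trial's main conclusion is at risk. It is not. The primary outcome is the annual screening rate over all modalities and does not condition on FIT. What is affected is an exploratory secondary measure, and the change is worth making because FIT adherence is a declared purpose of the study.

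**What to change.** Define the numerator and denominator, and base the initial-wave intervention-versus-control contrast on groups set independently of kit distribution:

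- (a) FIT completion among all patients seen who are due for screening, whether or not a kit was given, with due status fixed at the start of the year.
- (b) Repeat FIT among patients with a completed FIT in Year 0 who are due in Year 1, Wave 1 against Wave 2.

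Adjust both for the clinic's Year 0 rate where available, so that the baseline year is used and the contrast does not rest on seven against seven clinics in one year alone. Report kit-return proportions and later-year repeat FIT as descriptive process or maintenance measures.

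The cost is mainly wording. Individual-level data with a non-PHI patient ID are already planned, and test type, completion date and result are described as downloadable EMR fields. The small downside is that the Year 0 FIT cohort in (b) is smaller than the group of all FIT users, so its estimate will be less precise.
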